## Methods/design

### Hypothesis

The time to weaning from the HFNC will be shorter in the simultaneous reduction group compared to the group having flow or FiO_2_ reduction first, without increasing the weaning failure rate.

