### Randomization

A research coordinator will randomize the participants. An independent statistician will generate a list of random numbers. Eligible participants will be randomly assigned at a ratio of 1:1:1 to the flow reduction first (FR) group, the FiO_2_ reduction first (OR) group, or the simultaneous reduction (SR) group, in accordance with the predefined randomization list with a block size of 3. Information about the randomization will not be provided to the research supervisor, co-researcher, or patients. In the case of an emergency, co-researchers who are aware of the random assignments should avoid participating in future results analysis.

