### Outcome measures

The primary outcome is time to successful weaning from HFNC after 24 h of conversion to conventional oxygen therapy. The secondary outcomes will include the success or failure to wean off HFNC (within and after 24 h of conventional oxygen therapy), changes of arterial blood gas analyses (PaO_2_, PaCO_2_, and pH), intolerance rate, length of hospital stay, and in-hospital mortality.

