### Statistical analyses

Statistical analyses will be performed on both a per-protocol (PP) and an intention-to treat (ITT) basis. For the PP analysis, all participants who complete the study will be included to evaluate the primary and secondary outcomes. For the ITT analysis, all participants enrolled and randomized to one of the three groups will be included. In the interim analysis, if the *P* value is < 0.003, we will stop the study early, accepting the significance of the outcome. If not, we will recruit the remaining half of the subjects. Sub-group analysis according to the respiratory failure type (hypoxemic or hypercapnic) is planned. Unless otherwise specified, continuous variables will be expressed as mean plus standard deviations or median and categorical variables as percentages. Student’s *t* test will be used to compare continuous variables; the chi-square or Fisher’s exact test will be used to compare categorical variables. Unless otherwise stated, all tests are two-sided and performed at the 0.05 significance level. Analyses will be performed using SPSS 20.0 (IBM Corp., Armonk, NY, USA).

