## Discussion

The HFNC is usually applied in critically ill patients. We therefore considered a study design that would minimize the risk to the patients. First, we adopted strict criteria for both patient inclusion and the weaning process to ensure patient safety. Second, we decided to compare three stepwise weaning protocols for HFNC without including immediate withdrawal from HFNC. The potential advantage of immediate withdrawal is a considerable shortening of the weaning process. However, risk of failure and the need for reinstitution of the HFNC or intubation is a major concern. In contrast to immediate withdrawal, stepwise weaning may minimize atelectotrauma and gradually increase respiratory muscle strength without the associated risk of atelectasis. Finally, the attending physician and nurse are requested to assess the patient’s condition within 30 min of changing the HFNC setting. In this study, several clinical outcomes will be compared between these three groups. After completion of the study, we hope to be able to suggest the best strategy for the withdrawal of the HFNC in adult patients.

There are several strengths of this study design. This will be the first study to evaluate HFNC weaning strategies in an adult population. It has been designed as a prospective RCT, which is one of the most powerful study designs. Furthermore, we will not conduct any medical tests or interventions other than HFNC weaning in this study in order to reflect the actual clinical situation. There are also some limitations of this study, namely, the small sample size and the fact that the study will be conducted at a tertiary referral hospital. In addition, we will adopt 1-h interval weaning, which is slower than the HFNC weaning process used in clinical practice. However, it was a necessary choice to ensure patient safety. Given the shortcomings of this first study, further additional studies will eventually be required on larger scale.

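### A two-group t test at 0.05 per test is assigned to a three-arm trial whose primary contrast is not defined; run pairwise, it gives at least one false difference in about 9% to 12% of null trials

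*Protocol article*

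**What the plan says.** All of this is in the protocol article.

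- **Randomization:** "Eligible participants will be randomly assigned at a ratio of 1:1:1" to three groups, FR, OR and SR.
- **Outcome measures:** "The primary outcome is time to successful weaning from HFNC after 24 h of conversion to conventional oxygen therapy". This is a time, so it falls under the rule for continuous variables.
- **Statistical analyses:** Student's t "test will be used to compare continuous variables". Under a clause that allows for exceptions, "all tests are two-sided and performed at the 0.05 significance level". The only other threshold given is P < 0.003 at the interim analysis, with no comparison attached to it.
- **Hypothesis:** the time to weaning "will be shorter in the simultaneous reduction group compared to the group having flow or FiO_2_ reduction first", with no increase in weaning failure.
- **Discussion:** "several clinical outcomes will be compared between these three groups", and afterwards "we hope to be able to suggest the best strategy for the withdrawal of the HFNC in adult patients".

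**The concern.** A t test on three arms can be carried out only by testing pairs or by pooling two arms, and the article does not say which. The Hypothesis section reads most naturally as two comparisons that share the SR arm. The Discussion's aim of identifying the preferred strategy among three adds FR against OR. With each pair tested at 0.05, the error rate of the set exceeds 5%.

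The rule for success is also open. The article does not say whether SR must be shorter than one sequential strategy or both, and the error rate depends strongly on that. If the rule is chosen after the data are seen, the favourable comparison can be picked. The same gap affects early stopping: with two or three pairwise P values at the interim, any one of them could be taken as the P value that triggers the stop.

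**Working it through.** **Inputs.** Three equal arms (Randomization); two-sided 0.05 per test, critical value 1.960 (Statistical analyses); 30 per group (Sample size calculation); interim threshold 0.003 at half the subjects (Statistical analyses). No effect size or SD is needed, because the error rates are computed with all arms equal.

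**1. The plan's own figure.** Simulating one two-sample t test at two-sided 0.05 (400,000 null trials) gives 4.98% at 30 per group and 5.01% at 33 per group. The stated level is right for a single test.

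**2. Two comparisons, SR against FR and SR against OR.** The statistics share the SR arm, so their correlation is 0.5.
- P(both statistics below −1.960) = 0.00462.
- P(both significant, either direction) = 2 × 0.00462 + a negligible opposite-direction term = 0.0093.
- P(at least one) = 0.05 + 0.05 − 0.0093 = 0.0907, or **9.1%**. The t-test simulation at 30 per group also gives 9.07%.

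**3. All three pairs.** At least one |Z| exceeds 1.960 when the studentized range of three means exceeds 1.960 × √2 = 2.772. That probability is 0.1223, or **12.2%**. The simulation gives 12.2%. Treating the tests as independent would give 1 − 0.95² = 9.75% and 1 − 0.95³ = 14.3%, so the figures above already allow for the shared arms.

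**4. The directional claim, with all arms equal.**

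| Event | Calculation | Chance |
|---|---|---|
| SR falsely shorter, one comparison | 0.05 / 2 | 2.5% |
| SR falsely shorter than at least one comparator | 0.025 + 0.025 − 0.0046 | 4.5% |
| SR falsely shorter than both | joint probability from step 2 | 0.5% |
| Any arm falsely shorter than both others | 3 × 0.0046 | 1.4% |

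**5. Interim look at 0.003, applied to the same pairs.** The rates become about 9.3% (two comparisons) and 12.5% (three pairs), an addition of 0.2 to 0.3 points. For a single comparison, simulation gives 5.1%. The interim contributes little; the number of arms is what matters.

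**6. Per-test levels that hold the set at 5%.** For two SR comparisons: 0.025 (Bonferroni, actual family-wise rate 4.65%) or 0.0270 (Dunnett). For three pairs: 0.0167 (Bonferroni, 4.40%) or 0.0191 (Tukey).

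**7. Price in power.** At 30 per group and 80% power, the detectable standardised difference by t test is 0.736 at 0.05 and 0.814 at 0.025. The second is the worst case under Holm, whose larger P value is tested at 0.05 once the smaller has passed 0.025.

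**The case against.** Five points can be made for the plan.

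- **Per-test level.** The 0.05 is a default for each test and is correct as such; the article never claims 5% for the set. This stands. The comparison to draw is 9% to 12% for the set against 5% per test, not against a promised overall rate.
- **What the figure measures.** A reader might infer a 9% to 12% chance of wrongly declaring a winning strategy. The documents do not support that. The figure counts any false difference in either direction, and about half of the 9.1% consists of results with SR worse. A false finding that one arm beats both others occurs in 1.4% of null trials. The inflation remains for the directional claim: 4.5% against 2.5%.
- **Pooled reading.** The Hypothesis refers to the comparator in the singular, and the Abstract sets simultaneous against sequential reduction. If SR is compared with FR and OR pooled, a t test has the right form and the primary comparison keeps 5%. This reading is possible, but the Discussion's comparison among three groups points the other way, so the contrast is unsettled.
- **Left to the analysis plan.** An adjustment method may properly sit in an analysis plan that is not shown, and its absence here would not be a finding. But this article itself names a two-group test and a blanket default for a three-arm trial. An analysis plan that followed it would carry the problem forward.
- **Modest aims.** The Discussion admits the small sample and calls for larger studies, and whether distinct strategies need family-wise control is partly a matter of judgement. That lowers the severity. It does not remove the point, because the plan has a directional hypothesis and a rule to stop early on significance.

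**Conclusion.** The point holds as a should-fix. The article assigns a two-group test to a three-arm primary comparison and leaves the contrast and the success rule undefined. If tests are run pairwise at 0.05 with all arms equal, at least one false difference arises in about 9.1% of trials (two SR comparisons) or 12.2% (three pairs). SR is falsely shorter than at least one comparator in 4.5%. These figures assume equal arms and approximately normal test statistics.

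They do not apply under a pooled primary contrast, where the error stays at 5%, or under a rule that SR must beat both, where it is about 0.5% with all arms equal. The article adopts neither rule, so the figures show what is at stake in the choice rather than the error rate of a fully specified plan.

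**What to change.** For the primary outcome, adopt one of two schemes before any comparative data are seen.

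1. **Closed test.** Replace the t test with a three-group test at 0.05, and test pairs at 0.05 only if it is significant. This controls the error for exactly three groups: if all are equal, the global test guards at 5%; if only two are equal, a single true null hypothesis remains, tested at 5%. The loss of power is close to none, and FR against OR may be included.
2. **Two named comparisons.** Declare SR against FR and SR against OR confirmatory, jointly at 0.05 by Holm or Hochberg, and label FR against OR exploratory. The cost is slightly less power per comparison: under Holm, the detectable standardised difference rises from 0.74 to at most 0.81 at 30 per group and 80% power.

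Under either scheme, state whether SR must beat one comparator or both for the hypothesis to be supported, and name the comparison to which the interim P < 0.003 applies. If pooling FR and OR is what is meant, say so. The change is wording only and needs no extra patients.

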### Data and safety monitoring

The paper data collection sheets and signed informed consents will be stored in a locked cabinet, and the electronic database will be stored on password-protected secure severs. Any unanticipated adverse events that occur during the study will be reported to the Institutional.

Review Board in accordance with the procedures of Seoul National University Bundang Hospital, Korea. Any proposed revised study procedure will be submitted to the Seoul National University Bundang Hospital Institutional Review Board for approval and to

ClinicalTrials.gov. The data will be kept confidential with only limited access to research investigators.

## Discussion

The HFNC is usually applied in critically ill patients. We therefore considered a study design that would minimize the risk to the patients. First, we adopted strict criteria for both patient inclusion and the weaning process to ensure patient safety. Second, we decided to compare three stepwise weaning protocols for HFNC without including immediate withdrawal from HFNC. The potential advantage of immediate withdrawal is a considerable shortening of the weaning process. However, risk of failure and the need for reinstitution of the HFNC or intubation is a major concern. In contrast to immediate withdrawal, stepwise weaning may minimize atelectotrauma and gradually increase respiratory muscle strength without the associated risk of atelectasis. Finally, the attending physician and nurse are requested to assess the patient’s condition within 30 min of changing the HFNC setting. In this study, several clinical outcomes will be compared between these three groups. After completion of the study, we hope to be able to suggest the best strategy for the withdrawal of the HFNC in adult patients.

There are several strengths of this study design. This will be the first study to evaluate HFNC weaning strategies in an adult population. It has been designed as a prospective RCT, which is one of the most powerful study designs. Furthermore, we will not conduct any medical tests or interventions other than HFNC weaning in this study in order to reflect the actual clinical situation. There are also some limitations of this study, namely, the small sample size and the fact that the study will be conducted at a tertiary referral hospital. In addition, we will adopt 1-h interval weaning, which is slower than the HFNC weaning process used in clinical practice. However, it was a necessary choice to ensure patient safety. Given the shortcomings of this first study, further additional studies will eventually be required on larger scale.

## Trial status

Protocol version 1.0 (approval date 12 November 2018). This trial started recruiting in January 2019. Recruitment is expected to conclude by December 2020.

## Data Availability

Not applicable.

## Abbreviations

ABGA: Arterial blood gas analysis
ARDS: Acute respiratory distress syndrome
ECG: Electrocardiogram
FiO_2_: Fraction of inspired oxygen
FR: Flow reduction
HFNC: High-flow nasal cannula
ICU: Intensive care unit
ITT: Intention to treat
NIV: Non-invasive ventilation
OR: Reduction in fraction of inspired oxygen
PaCO_2_: Partial pressure of carbon dioxide
PaO_2_: Partial pressure of oxygen
PP: Per protocol
RCT: Randomized controlled trial
SBP: Systolic blood pressure
SD: Standard deviation
SNUBH: Seoul National University Bundang Hospital
SR: Simultaneous reduction
